## Abstract

**Background::**

Mitral commissural prolapse or flail, characterized by intricate and diverse anatomical features, poses a significant challenge in mitral transcatheter edge-to-edge repair (M-TEER). Previous studies have largely focused on central mitral regurgitation with favorable valve anatomy or a general broad spectrum of complex mitral regurgitation. However, no established approach is currently available for M-TEER in commissural degenerative mitral regurgitation (DMR).

**Methods::**

Therefore, this study aimed to evaluate the efficacy and safety of a novel morphology classification-guided M-TEER strategy for treating commissural DMR using the MitraClip system. This prospective, multicenter, single-arm, objective performance criteria study involved 12 experienced centers in Asia, primarily located in China. Patients with symptomatic moderate-to-severe (3+) and severe (4+) native DMR and commissural involvement were stratified into three morphological categories based on an echocardiographic core laboratory analysis, and tailored M-TEER strategies were proposed. The primary endpoint is the proportion of patients achieving a mitral regurgitation (MR) grade of ≤1+ without repeat mitral intervention at one-year follow-up. Clinical, echocardiographic, functional, and quality-of-life outcomes were assessed over one year.

**Results::**

Based on statistical power calculations, a total of 148 patients are required to achieve adequate power to test the primary efficacy hypothesis, accounting for an estimated 10% attrition rate at 12 months.

**Conclusions::**

The morphology classification system enhances M-TEER for commissural DMR by addressing the unique challenges of this approach, enabling tailored interventions that optimize procedural success and patient outcomes.

**Clinical Trial Registration::**

ChiCTR2400090258, https://www.chictr.org.cn/showproj.html?proj=239191.

## 1. Introduction

Mitral regurgitation (MR) is a prevalent valvular heart condition, with 
degenerative MR (DMR) affecting at least 24 million people worldwide [1]. Within 
the spectrum of DMR, commissural lesions represent a significant subset, 
characterized by prolapse or flail involving the mitral valve commissures. These 
lesions, while less common than central scallop prolapse, pose unique challenges 
due to their anatomical location and the complex interplay of the mitral valve 
apparatus. However, epidemiological studies suggest that commissural DMR is often 
under-recognized and can be associated with more advanced disease at the time of 
diagnosis, partly due to the subtle and variable presentation on standard 
echocardiographic evaluation [2].

Mitral Transcatheter Edge-to-Edge Repair (M-TEER) therapy has revolutionized the 
treatment of MR by offering a minimally invasive alternative to surgery [3, 4]. 
However, the treatment of commissural lesions remains particularly challenging. 
Unique anatomical factors—such as the difficulty in accessing and visualizing 
the commissural regions—combined with the technical demands of the procedure 
and devicerelated challenges, including the need for transseptal puncture 
(transfemoral MTEER), the long access route, the risk of clip entanglement with 
chordae tendineae, and the limited grasping range of current devices, contribute 
to the higher rates of residual or recurrent MR observed in this subgroup [5]. 
Notably, prior literature has reported that, among patients with commissural DMR 
treated with M-TEER, only 45% achieved MR ≤1+ at discharge and 33.3% at 
3-year follow-up [6], underscoring the procedural complexity and suboptimal 
long-term durability in this challenging subset. Additionally, the lack of 
standardized classification systems and tailored procedural strategies for 
commissural DMR has hindered the optimization of M-TEER outcomes. Besides, some 
investigators have proposed an adjunctive technique involving MitraClip 
implantation followed by the placement of an Amplatzer Vascular Plug (AVP) II 
between the commissure and the MitraClip to address residual regurgitation in 
commissural DMR [7]. While technically feasible, this approach has been 
associated with a relatively high incidence of post-procedural hemolysis [8], 
which has limited its widespread adoption. Furthermore, patients with commissural 
lesions are frequently excluded from clinical trials or are represented by a 
small proportion of the study population, which limits the generalizability of 
current treatment guidelines.

Considering the lack of evidence on M-TEER therapy for commissural DMR, we 
designed a prospective, multicenter, single-arm clinical investigation. The 
Mitral Valve Transcatheter Edge-to-Edge Repair for Patients with Commissural 
Degenerative Mitral Regurgitation (TEER-CD) study aims to address these gaps by 
focusing on the development and validation of a novel morphological 
classification system specifically designed for commissural DMR. This system is 
designed to standardize patient selection and procedural techniques, thereby 
potentially improving the safety and efficacy of M-TEER in this challenging 
patient population. By doing so, the study seeks to broaden the applicability of 
M-TEER and provide a much-needed evidence base for the treatment of commissural 
DMR.

## 2. Materials and Methods

### 2.1 Study Design and Objectives

TEER-CD (registered at https://www.chictr.org.cn/, identifier ChiCTR2400090258) 
is a prospective, multicenter, single-arm, objective performance criteria 
clinical trial designed to rigorously evaluate the safety and efficacy of a novel 
morphological classification-guided M-TEER approach for patients afflicted with 
commissural DMR. This study may represent a further advancement in the field of 
interventional cardiology, focusing on a patient population that has historically 
been challenging to treat with conventional M-TEER methods. The study aims to 
demonstrate that this novel strategy can achieve safety and effectiveness 
comparable to that observed for central DMR using current standard of care M-TEER 
approaches.

The primary objective of this trial is to assess the safety and effectiveness of 
the MitraClip system (Abbott, Abbott Park, IL, USA) in patients with symptomatic, 
moderate-to-severe (3+) or severe (4+) native commissural DMR. The trial is 
designed to demonstrate that outcomes with the novel morphological 
classificationguided approach for commissural DMR are equivalent or similar to 
those achieved for central DMR, consistent with American College of 
Cardiology/American Heart Association (ACC/AHA) and European Society of 
Cardiology (ESC) guideline recommendations [9, 10].

The TEER-CD trial design and endpoints were developed by the study investigators 
and steering committee in accordance with the definitions outlined by the Mitral 
Valve Academic Research Consortium (MVARC) [11]. The TEER-CD trial is jointly 
funded by Beijing Anzhen Hospital and Abbott Medical. Participating centers have 
obtained approval from an institutional ethics committee. Informed consent forms 
are provided to the subjects in the trial.

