### 2.9 Statistical Considerations

#### 2.9.1 Sample Size Calculation

The primary endpoint of this study is the proportion of patients achieving a MR 
grade of ≤1+ without repeat mitral intervention at 1-year follow-up. The 
study is designed as a single-arm, objective performance goal (OPG) trial with 
the following statistical hypotheses:

*H₀: P_𝑇_
≤ P₀*

*H₁: P_𝑇_
> P₀*

where *P*_𝑇_ represents the expected primary endpoint rate in this 
study, and *P₀* denotes the target performance level derived from previous 
literature.

Based on our center’s retrospective data and relevant published studies [16], 
the expected rate of the primary endpoint (*P*_𝑇_) was set at 85%. The 
target performance level (*P₀*) was set at 75%, reflecting clinically 
acceptable outcomes reported for complex MR populations in previous trials [17].

Using a one-sided significance level (α) of 0.025, a statistical power 
(1–β) of 80%, and assuming a 10% dropout rate at 12-month follow-up, 
the required sample size was calculated to be 148 patients. The sample size 
calculation was performed using the formula for a one-sample proportion test 
against a performance goal:

$$n=\frac{{\left[Z_{1-\alpha }\cdot \sqrt{P_{0}\,\left(1-P_{0}\right)}+Z_{1-\beta }\cdot \sqrt{P_{T}\,\left(1-P_{T}\right)}\right]}^{2}}{{\left(P_{T}-P_{0}\right)}^{2}}$$

where *Z*_1-α_ = 1.96 for a onesided α of 0.025, and 
*Z*_1-β_ = 0.84 for 80% power. 

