#### 2.9.3 Statistical Analysis

Baseline characteristics, procedural data, and follow-up outcomes will be 
summarized using descriptive statistics. Continuous variables will be presented 
as means ± standard deviations (SD) if normally distributed, or as medians 
with interquartile ranges (IQR) if non-normally distributed. Categorical 
variables will be expressed as frequencies and percentages.

The primary efficacy analysis will be conducted in the ITT population using a 
one-sample proportion Z-test to evaluate whether the proportion of patients 
achieving MR ≤1+ at 12 months exceeds the prespecified OPG of 75%. A 
one-sided significance level of 0.025 will be applied to test the null hypothesis 
that the success rate is less than or equal to the OPG.

Secondary endpoints will be analyzed descriptively. Comparisons of continuous 
variables between baseline and follow-up will use paired *t*-tests or 
Wilcoxon signed-rank tests based on data distribution. Categorical variables will 
be compared using McNemar’s test or Cochran’s Q test, as appropriate. 
Time-to-event outcomes will be analyzed using Kaplan–Meier estimates, with 
median survival times and event-free rates calculated at 30 days, 6 months, and 
12 months. Log-rank tests may be applied for subgroup comparisons where relevant.

To assess long-term durability, all subjects will be followed for up to five 
years. A secondary Bayesian analysis will be performed to estimate the posterior 
probability of sustained therapeutic success (defined as MR ≤1+ without 
mitral valve replacement or reintervention). This approach enables dynamic 
updating of treatment effect estimates over time and offers further insight into 
outcomes beyond the 12-month endpoint.

Predefined subgroup analyses will be performed according to the three 
morphological subtypes to evaluate the efficacy and safety of the 
classification-guided M-TEER strategy. Due to distinct procedural approaches and 
expected small sample sizes within subgroups, a dual analytic strategy will be 
employed: exact tests will be used for small-sample inference, while Bayesian 
methods will provide probabilistic estimations with credible intervals, 
incorporating prior knowledge to enhance robustness.

Sensitivity analyses will be conducted to evaluate the stability of the primary 
outcome results. These will include analyses based on the PP 
population—excluding major protocol deviations—and scenario-based imputations 

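### Section 2.1 promises safety and effectiveness comparable to central DMR, but the only confirmatory test is success above a 75% goal taken from complex MR

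*Protocol article*

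**What the plan says.** Section 2.1 states the aim twice in confirmatory terms. The strategy is to achieve safety and effectiveness "comparable to that observed for central DMR using current standard of care M-TEER" approaches. The trial is then described as designed to demonstrate that outcomes with the "classificationguided approach for commissural DMR are equivalent or similar to" those in central DMR. Between these two statements, the sentence labelled as the primary objective says the trial will assess the safety and effectiveness of the device.

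Section 2.9.1 sets the hypotheses. The "study is designed as a single-arm, objective performance goal (OPG) trial with" H0: P_T ≤ P0 against H1: P_T > P0. The goal P0 "was set at 75%, reflecting clinically" "acceptable outcomes reported for complex MR populations in previous trials". The expected rate P_T is 85%, sourced as follows: "Based on our center’s retrospective data and relevant published studies [16". Section 2.9.3 tests the 12-month rate against 75% with a one-sample Z-test at one-sided 0.025 in the ITT population.

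Table 2 lists one primary endpoint, for efficacy. Every safety endpoint is in the secondary group, and section 2.9.3 says: "Secondary endpoints will be analyzed descriptively". No safety goal appears.

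**The concern.** The objective and the hypothesis concern different comparators. The objective names central DMR, while the test uses a threshold drawn from complex MR. The article's own Background keeps these apart: it distinguishes earlier work on central regurgitation with favourable anatomy from work on a broad range of complex regurgitation. Rejecting H0 therefore does not bear on the comparison that section 2.1 promises.

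The type of claim differs too. Equivalence or similarity needs a reference rate and a margin, and the article has neither. For safety the gap is wider, because section 2.1 includes safety in what is to be demonstrated but no safety hypothesis of any kind is planned.

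At stake is what may be concluded after a positive result. Section 3.2 expects the study could help refine treatment guidelines. A reader who takes section 2.1 at its word could report a win as comparable efficacy and safety when neither had been tested.

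**Working it through.** **Inputs (section 2.9.1).** P0 = 0.75, P_T = 0.85, one-sided alpha 0.025, power 80%, dropout 10%, stated N = 148.

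**Step 1: reproduce the plan's figure.**

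n = [z(1−α)·√(P0(1−P0)) + z(1−β)·√(P_T(1−P_T))]² / (P_T − P0)²

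- With unrounded z values: [1.95996 × 0.43301 + 0.84162 × 0.35707]² / 0.10² = [0.84869 + 0.30052]² / 0.01 = 132.07, so 133 evaluable.
- 133 / 0.9 = 147.8, so 148 enrolled. The stated figure reproduces.
- With the article's rounded 1.96 and 0.84: 131.94, so 132, and 132 / 0.9 gives 147. The difference of one is rounding.

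**Step 2: what a pass establishes.** The Z-test passes when (x/n − 0.75) / √(0.75 × 0.25 / n) ≥ 1.96.

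| Patients analysed | Smallest passing count | Observed rate | Wilson 95% CI | Exact one-sided alpha | Power at 85% |
|---|---|---|---|---|---|
| 133 (evaluable) | 110 | 82.7% | 75.4% to 88.2% | 0.022 | 0.808 |
| 148 (all enrolled are treated and counted) | 122 | 82.4% | 75.5% to 87.7% | 0.020 | 0.839 |

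In both cases the lower limit at a bare pass is about 75%. If the true rate were 80%, the trial would still pass with probability 0.25 (n = 133) or 0.27 (n = 148).

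**Step 3: the deficit against central DMR left open.** This is the central-DMR rate C minus about 75 points. The article gives no C, so the values below are assumptions.

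| Assumed C | Deficit not excluded at a bare pass |
|---|---|
| 80% | 5 points |
| 85% | 10 points |
| 90% | 15 points |
| 95% | 20 points |

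A clearer win narrows this somewhat. At 113/133 (85.0%, the planned rate) the Wilson lower limit is 77.9%, so each entry falls by about 3 points.

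**Step 4: other planned analyses.** Section 2.9.3 also lists paired tests, McNemar and Cochran tests, possible log-rank subgroup comparisons, exact and Bayesian subgroup analyses, and a Bayesian durability analysis. None uses a central-DMR reference, and none sets a safety goal.

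**Step 5: what keeping the claim could require for efficacy.** Set goal = C − M, with C and the margin M both assumed, a true rate of 85%, and the same formula, alpha, power and dropout.

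| Goal | Example C and M | Evaluable | Enrolled |
|---|---|---|---|
| 70% | 80% and 10, or 85% and 15 | 64 | 72 |
| 75% | 80% and 5, 85% and 10, or 90% and 15 | 133 | 148 |
| 80% | 85% and 5, or 90% and 10 | 471 | 524 |
| 85% | 90% and 5 | not attainable at a true rate of 85% | – |

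**The case against.** The strongest reply is that this is wording around a sound test. The sentence labelled as the primary objective says only that safety and effectiveness will be assessed. The hypotheses, test, alpha and sample size agree with one another. Section 3.3 justifies the goal by the lack of an established comparator for this subset and calls the secondary analyses descriptive and exploratory. Section 3.4 concedes that a single arm limits direct comparison with other treatments. The abstract's aim and both conclusions sections make no mention of central DMR. All of this stands and lowers the risk of misreading, but none of it withdraws the two statements in section 2.1.

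A second reply is that a single-arm goal can act as a non-inferiority bound, and that 75% is what a central rate of 85% with a 10-point margin would give. That is true as arithmetic, but section 2.9.1 gives a different derivation.

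A third is that secondary safety endpoints are normal. They are: two 12-month composites and a safety population are prespecified, and nothing is wrong with that unless comparable safety is claimed.

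Four stronger readings are tempting, and the document does not support them:
- That the test against 75% is the only test. It is the only confirmatory one.
- That 75% is the wrong number. The article shows only that it was not derived from central DMR.
- That a deficit of 10 to 20 points is a documented quantity. It depends on an assumed central rate, and at 80% it is 5 points.
- That the article draws an equivalence conclusion. It states the aim in section 2.1, but its conclusions do not claim equivalence.

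**Conclusion.** The point holds as a mismatch between the objective in section 2.1 and the hypothesis in section 2.9.1. Rejecting H0 shows that 12-month success in commissural DMR exceeds 75%. It cannot support comparability with central DMR for efficacy, and no planned analysis can support it for safety.

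The size of the efficacy gap rests on assumed central-DMR rates of 80% to 95% and on a bare pass. For safety, no deficit of any size is tested.

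The sample size and the test are valid for the question they address. This is not a detail to leave to an unseen analysis plan, because the article states both the aim and the hypothesis and the two do not match. It should be corrected because it determines what a positive trial may claim.

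**What to change.** Restate the objective in section 2.1 along these lines: to show that the 12-month success rate in commissural DMR exceeds a performance goal of 75% derived from complex MR populations, with safety described using two-sided 95% confidence intervals. Delete both statements that outcomes are to be shown comparable, equivalent or similar to central DMR. The cost is a narrower claim. Enrolment, endpoint and test do not change.

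Keeping the comparability claim is a different and larger change. It needs a cited central-DMR rate, a justified margin, a P0 derived from the two, a safety goal and a recalculated sample size. Under the assumptions shown above, enrolment for efficacy alone ranges from 72 to 524, and some choices are not attainable at a true rate of 85%. The safety goal would need its own calculation.

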### 2.2 Imaging Protocol

#### Determination of Commissural Degenerative Mitral Regurgitation

MR associated with commissural degenerative disease is characterized by specific 
anatomical abnormalities primarily involving the mitral valve commissures. The 
commissures, where the anterior and posterior mitral leaflets meet, are critical 
points of coaptation during systole and are prone to degenerative changes [2, 12].

The anatomical determination of mitral commissures is essential for accurate 
diagnosis and treatment planning. The mitral valve is separated by two 
commissures: the anterolateral commissure (AC) and the posteromedial commissure 
(PC). These commissures are identified by the characteristic chordae tendineae 
that merge, creating a fan-like appearance, and are essential for leaflet 
coaptation [2]. In clinical practice, the cleavage segment that separates the 
anterior leaflet from the posterior leaflet is used as an imaging approximation 
for the true anatomic commissures, especially when individual chordae tendineae 
attachments are difficult to discern via transesophageal echocardiography (TEE).

The morphological abnormalities defining commissural DMR include prolapse or 
flail of the commissural segments. The diagnosis is confirmed by the observation 
of abnormal protrusion of the commissural segment into the left atrium during 
systole due to elongation or rupture of the commissural chordae tendineae. This 
is evident in both two-dimensional (2D) and three-dimensional (3D) 
echocardiographic imaging, which is crucial for the classification and subsequent 
procedural strategy for M-TEER (Fig. 1, Ref. [13]).

**Fig. 1. S2.F1:**
[figure not shown]
**Definition of commissural degenerative mitral regurgitation**. 
(A) Commissures, where anterior and posterior mitral leaflets converge during 
systole, typically form a Y-shaped structure by joining three segments (e.g., 
A1-anterolateral commissure-P1 or A3-posteromedial commissure-P3), distinguished 
by fanlike chordae tendineae stemming from anterolateral and posteromedial 
papillary muscles. Given the difficulty in distinguishing individual chordae on 
transesophageal echocardiography, the cleavage segment that separates the 
anterior leaflet from the posterior leaflet is used as imaging for anterolateral 
and posteromedial commissure approximation of true anatomic commissures. (B) The 
protrusion of the commissural segment into the left atrium during systole or (C) 
the rupture of commissural chordae tendineae characterizes commissural prolapse 
or flail [13]. AV, aortic valve.

A standardized TEE protocol was implemented at each participating site and 
monitored by the echocardiographic core laboratory (ECL). Initial imaging was 
conducted at the mid-esophageal level to assess the mitral valve. If this level 
did not yield high-quality images, imaging at the transgastric level was 
mandated. The protocol included 2D single-plane and simultaneous multiplane 
imaging to delineate the pathology of MR. The primary reference view, the 
mid-esophageal mitral commissural view, was primarily used to evaluate the 
distribution of the regurgitant jet. The secondary view, the long axis view, was 
aligned perpendicular to the mitral valve coaptation line to further characterize 
the regurgitant pathology. 3D TEE enhanced with multiplanar reconstruction 
provided a detailed visualization of the mitral valve anatomy. Color Doppler 
imaging was employed across these views to accurately localize the origins of the 
mitral regurgitant jets (Fig. 2, Ref. [13]) [14]. The severity of MR was assessed by the ECL 
at baseline and follow-up using a comprehensive analysis of quantitative and 
semiquantitative criteria according to the American Society of Echocardiography 
[15].

**Fig. 2. S2.F2:**
[figure not shown]
**Imaging protocol for mitral valve commissural disease**. (A) 
Illustration of the mitral valve (MV), surgeon’s view in the “clock-face plane” 
with the aortic valve (AV) at the 12 o’clock. Transesophageal echocardiography is 
used to identify mitral commissural (bicommisural) view anatomically optimized 
the MV plane (~50°–70°, the red dash line), 
and long axis (LAX) view best clarified MV coaptation plane, such as 
~120°–150° for central segments (the green dash 
line), >~150° for lateral segments (the yellow dash 
line), and <~130° for medial segments (the blue dash 
line). (B) Simultaneous biplane imaging permits the use of a dual screen to 
display two real-time two-dimensional images simultaneously. The first (primary) 
image of the MV commissure view can be used as the reference view, with the 
second view, LAX view rotated from 0° to 180° from the primary 
view to sweep the interrogation of the MV coaptation (central, lateral, and 
medial tilts). (C) Example of biplane imaging with (D) color Doppler 
simultaneously displays bicommissural view 
(~50°–70°) and modified LAX view to identify 
the posteromedial commissural lesions. (E) Example of biplane imaging with (F) 
color Doppler simultaneously displays bicommissural view 
(~50°–70°) and modified LAX view to identify 
anterolateral commissural lesions. (G) Three-dimensional rendered enface view 
with multiplanar reconstruction technique is used to determine the precise 
mechanism of mitral regurgitation and morphological characteristics of the MV [13]. 
3D, 3-dimensional; AC, anterolateral commissure; Ant, anterior; Lat, lateral; MC, 
mitral commissure; ME, midesophageal; Med, medial; MR, mitral regurgitation; MV, 
mitral valve; Post, posterior; SAX, short axis; PC, posteromedial commissure.

